**6. PARTICIPANTS ENROLLMENT**

Before initiating specific research activities/procedures, all participants must personally sign the digital informed consent form. Each participant has been assigned a unique identification number, which will be used throughout the study to identify the individual and must be used in all research-related documents pertaining to that participant. This identification number must remain unchanged throughout the study; it should not be altered, including during re-screening of participants, after the initial assignment.

**Confirmation of TGW identity:** The study participants' transgender female identity is verified through a logical screening process using self-identified gender questions in the baseline questionnaire. Researchers rigorously assess the identity of the participants. If there are doubts about the identity of a participant, an additional identity confirmation questionnaire is sent, which includes questions about transgender-related knowledge. Additionally, the following methods are used to corroborate their identity: contacting the participant's recruiter to request identity verification evidence, reviewing the participant's social media posts for identity-related clues or evidence, and requesting the participant to provide recent photos of themselves presenting in feminine attire.

When the researchers determine that a participant meets the inclusion criteria, the investigator should record this decision and the date in the digital Case Report Form (CRF).

**7. STUDY PROCEDURES**

**7.1 Baseline**

Eligible participants will undergo an online informed consent process. After agreeing to participate in the study, participants will be invited to complete a questionnaire survey. The demographic and behavioural characteristics of the two groups of participants will be collected through an online survey platform (<https://jinshuju.net/home>).

**7.2 Follow Up**

For all participants, the study duration is six months from enrolment. All participants will receive follow-up surveys based on the online questionnaire platform at three and six months after enrolment.

**7.3 Intervention Contents**

**7.3.1 Quadruplex Self-Testing Package**

The quadruplex self-testing kits to be used (Wondlfo Guangzhou, China) are finger stick-based, which can detect antibodies of HIV-1, Treponema pallidum (TP), HBV, and HCV in blood specimens at 6 weeks after infection. The test kit will be packaged together with the necessary consumables (disposable retractable lancet, alcohol pad, capillary tube, Wondlfo solution, and a sealed bandage). Each package will include the corresponding identification number and instructions for the testing procedure, result interpretation, and result uploading. (Figure 2, 3).

[figure not shown]

**Figure 2 HIV self-testing package details**

[figure not shown]

**Figure 3 HIV self-testing instructions**

**7.3.2 Online intervention**

HIV-related health information will be simultaneously sent to the intervention group and the control group via WeChat, with one message sent at enrolment and another message sent three months after enrolment. The content of the messages will include local testing locations for HIV (such as CDCs, hospitals, and CBO testing groups), information on HIV transmission routes, and prevention measures for HIV (such as condom use and PrEP).

**7.4 Intervention Procedures**

After including TGW who test negative for HIV and meet the eligibility criteria, they will be randomly assigned to the intervention group and the control group in a 1:1 ratio. Based on participants' needs, the intervention group will have the opportunity to apply for free HIV self-testing (HIVST) kits and mailing services every three months (via WeChat). Participants can request to receive 1-5 self-testing kits based on their own needs, and they are encouraged to share the HIVST kits with their partners. HIV-related health information will be regularly sent to both the intervention and control groups at predetermined intervals (at enrolment and three months after enrolment). Follow-up surveys will be conducted, and electronic questionnaires will be filled out at three months and six months after enrolment. To protect personal privacy, all HIV self-testing kits mailed to participants will be discreetly packaged in an unmarked box along with the instructions. Each self-testing kit will be assigned a unique code for future tracking and result retrieval. Users of the self-testing kits can scan the QR code on the instructions, take a photo of the self-test result, and anonymously upload it to the online platform (created through the online questionnaire platform: <https://jinshuju.net/home>).

**7.5 Measures of Different HIV Testing Results**

During the implementation of the study, researchers provide a series of counselling services to the participants before and after testing. They promptly review the result images uploaded by users of the self-testing kits. If the self-test result shows positive for HIV, the researchers will contact the individual immediately to provide appropriate counselling and referral services, including explaining the test result and referring them to medical institutions or Center for Disease Control and Prevention for HIV confirmatory testing, CD4 testing, and antiretroviral treatment services. If the HIV self-test result is negative, the participants will receive information about regular HIV testing and safe sexual behaviour.

**7.6 Questionnaire Contents**

The baseline questionnaire includes demographic characteristics (age, educational level, marital status, monthly income, etc.) and behavioural characteristics in the past three months (frequency of HIV self-testing kit use, frequency of HIV testing at venues, types and number of sexual partners in the past three months, condom use, drug use, inquiring about the HIV infection status of sexual partners, history of sexually transmitted diseases, age at first sexual intercourse, sexual orientation, etc.).

The follow-up surveys also include information about HIV testing results (whether disclosed to sexual partners), the number of HIVST kits shared with sexual partners, types of sexual partners, and knowledge of sexual partners' HIV infection status. Sexual partners who undergo HIV testing will be invited to complete a questionnaire, which includes demographic and behavioural characteristics, as well as the results of their most recent HIV test.

**8. WITHDRAWAL FROM THE STUDY**

**8.1 Decision to Withdraw from Participants or Investigators**

Participants have the right to withdraw from this study at any time for any reason without affecting their future rights to medical care and services at the institution. Participants may refuse to continue receiving the intervention at any time during the study, but can still remain involved in the research. Researchers may also decide to withdraw participants from the intervention measures, study procedures, or the entire study at any time before its completion.

**8.2 Reasons for Removal from Study**

Reasons for removal from the study include any of the following:

- Participants request
- Safety concern (such as concerns about being harmed by sexual partners)
- Withdrawal of consent from the study
- HIV seroconversion
- Loss of follow-up or death
- The decision by the investigator (If participants request test kits for purposes other than testing, such as obtaining HIV self-test kits for the purpose of selling them, rather than using them for their own and their sexual partners' HIV testing)

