**10. STATISTICAL CONSIDERATIONS**

**10.1 Intention-to-Treat Set (ITT) Population**

The Intention-to-Treat Set (ITT) is defined as all randomized participants. The primary analysis population for all efficacy endpoints will be the Full Analysis Set (FAS) population.

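### Section 8.2 takes people out of the whole study for seroconversion and for kit misuse, so outcomes would go missing for reasons tied to arm and to testing behaviour

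*Protocol*

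**What the plan says.** Section 8.2 opens with "Reasons for removal from the study include any of the following". Its list includes "HIV seroconversion" and an investigator decision, explained by "If participants request test kits for purposes other than testing, such as obtaining HIV self-test kits for the purpose of selling them". Both therefore operate at the level of the study.

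Section 8.1 is more graded. It says "Participants may refuse to continue receiving the intervention at any time during the study, but can still remain involved in the research", and it lets researchers withdraw someone from the intervention, from study procedures or from the study as a whole. Section 8.2 does not refer back to these levels.

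Sections 3.1 and 7.4 offer kits to the intervention group only. Section 7.5 says of the researchers "They promptly review the result images uploaded by users of the self-testing kits", and describes no matching route for a control participant's positive result. Follow-up in section 7.2 is by questionnaire: "All participants will receive follow-up surveys based on the online questionnaire platform at three and six months after enrolment". No HIV test is scheduled in both arms during follow-up. Section 5 states that staff of the community organisations and participants are not blinded.

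On analysis, section 10.1 states "The Intention-to-Treat Set (ITT) is defined as all randomized participants", and 10.3 bases all effect analyses on that set. Section 10.1 also names a Full Analysis Set, which the protocol does not define. Section 10.3.2 plans covariance analysis plus a mixed model for the primary outcome, and 10.3.3 presents imputation as a sensitivity analysis.

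**The concern.** The primary outcome is a count of HIV tests, which section 10.3.1 takes from participants' reports. The questionnaire in Appendix C asks about the past three months. Someone removed before a survey has no questionnaire value for that period.

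The two grounds are not neutral between arms. Removal for kit misuse is a discretionary decision, made after randomisation in an open-label trial, and it exists in one arm only. It also concerns what people do with test kits, which is close to the outcome itself. Known seroconversion depends on being tested, which is the behaviour that the intervention is meant to increase.

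At stake is whether the participants with outcome data in the two arms remain comparable as randomised.

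**Working it through.** **1. The plan's own figure.** Inputs from 10.4 and 10.4.1: difference 0.35 tests per three months, SD 1, correlation 0.2, two time points with compound symmetry, two-sided alpha 0.05, power 0.90.

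- SD of the mean of two measurements = √((1 + 0.2)/2) = 0.7746.
- This gives 103 per group with power 0.9002, matching the stated 103 and 0.90019.
- 103/(1 − 0.10) = 114.4, rounded up to 115, as stated.

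The sample size is correct and is not in dispute.

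**2. Where each removal can arise.**

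| Ground in 8.2 | Intervention arm | Control arm |
|---|---|---|
| Kits requested for other purposes | Possible | Not possible: no kits offered (3.1, 7.4) |
| Seroconversion | Found from uploaded images (7.5), venue tests or surveys | Found from venue tests or surveys; no image route described |

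The first row follows directly from the text. The second is an inference: detection is likely to be more frequent in the intervention arm, but it is not confined to it.

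**3. Size of a shift.** The protocol gives no removal rate and no testing rate among those removed, so both are assumptions. Let a fraction *f* of the intervention arm be removed, with a mean *g* tests per three months below the mean *m* of those kept. Then

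mean(all) = (1 − f)·m + f·(m − g) = m − f·g,

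so the mean of those kept exceeds that of the full arm by f·g. If those removed test more, the sign reverses. This assumes that both survey values are lost; removal after the month-3 survey would lose only the second.

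For type I error I used the sample-size model, 115 per arm and 10% other dropout in both arms:

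SE = 0.7746 × √(1/[115(0.9 − f)] + 1/[115 × 0.9])

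type I error = Φ(−1.96 + f·g/SE) + Φ(−1.96 − f·g/SE)

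For f = 5% and g = 1, the numbers left are 97.75 and 103.5, SE = 0.109, f·g/SE = 0.458 and the error is 0.074.

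| f | g | Shift (tests) | Share of 0.35 | Two-sided type I error |
|---|---|---|---|---|
| 1% | 0.5 | 0.005 | 1.4% | 0.050 |
| 1% | 1 | 0.01 | 2.9% | 0.051 |
| 2% | 0.5 | 0.01 | 2.9% | 0.051 |
| 2% | 1 | 0.02 | 5.7% | 0.054 |
| 5% | 0.5 | 0.025 | 7.1% | 0.056 |
| 5% | 1 | 0.05 | 14.3% | 0.074 |
| 10% | 0.5 | 0.05 | 14.3% | 0.074 |
| 10% | 1 | 0.10 | 28.6% | 0.147 |

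**4. Power.** With the same dropout, power is 0.902 with no extra removals, and 0.898, 0.893 and 0.884 with 2%, 5% and 10% extra removals in the intervention arm. Lost power is minor; the issue is bias.

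**5. Number of seroconverters.** At an assumed incidence of 1–5 per 100 person-years, 115 × 0.5 years × 0.01 to 0.05 = 0.6 to 2.9 people per arm.

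**The case against.** **The intention-to-treat set is not redefined.** A reader might infer that 8.2 breaks the intention-to-treat principle outright. The documents do not support that: the set remains everyone randomised, and no passage drops removed participants from it or deletes their data. What remains is a missing-data problem. The mixed model can use a month-3 value when month 6 is absent, imputation is planned, and details may sit in a statistical analysis plan that is not shown. But no analysis plan can recover surveys that were never sent, and these methods ordinarily rely on the observed data explaining the missingness, which is doubtful when removal follows from kit misuse.

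**Section 8.1 already allows the milder course.** Researchers may withdraw someone from the intervention alone, and section 7.2 promises surveys to all participants. This stands, and it makes the repair small. Still, 8.2 places both grounds under removal from the study and does not say that surveys continue.

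**The direction is open.** It is tempting to say that the remaining intervention arm is enriched for genuine testers, so the effect is inflated. That holds only if those removed for misuse test less than those kept. They may test at venues, or over-report. Losing seroconverters together with their tests pulls the other way. A net upward bias is not established.

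**The larger figures are pessimistic.** Removing 5–10% for misuse would be half to all of the planned 10% dropout, and a gap of one test is a full planning SD. Kits are limited to five per request, with links given only at enrolment and month 3. At 1–2% removal the shift is at most 0.02 tests.

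**The diagnosing test may be on record.** An uploaded positive image reaches staff before any removal, and nothing says that it is discarded. Equally, nothing says that it counts once the participant is removed.

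**Conclusion.** The point holds in a limited form. Followed as written, section 8.2 ends study participation for one reason that can occur only in the intervention arm and for another that is likely to be detected more often there. Both are related to testing, and the protocol does not provide for outcome collection afterwards. This sits badly with the commitment in 10.1 and 10.3 to analyse everyone randomised.

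The size is unknown. Over assumed removals of 1–10% of the intervention arm and an assumed gap of 0.5–1 test, the shift is about 0.005–0.10 tests, or 1–29% of the 0.35 target, in either direction. The upper end should not be read as an expected value, and seroconversion should not be described as an intervention-only reason. The case for change is that the loss of data is avoidable at almost no cost.

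**What to change.** Reconcile 8.2 with 8.1, 10.1 and 10.3. For seroconversion and kit misuse only:

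- Separate ending kit supply from ending data collection. Whether and when supply ends stays with the investigators; this point takes no view on it.
- Continue to invite these participants to the month-3 and month-6 online surveys where consent allows, and analyse them in the arm to which they were randomised.
- State that tests up to and including the diagnosing test count towards the outcome. This is a choice of estimand and should be written down as one.
- Report removals by arm and by reason.

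Leave the safety-concern, participant-request and consent-withdrawal grounds as they are. In 10.1, make clear that the Full Analysis Set does not exclude the participants concerned.

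The cost is an edited list and a few extra online surveys, with no new procedure.

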**9. ADVERSE EVENTS**

In the vast majority of cases, fingerstick blood collection conducted in this project is safe. However, in rare instances, some individuals may experience discomfort such as dizziness, and in extremely rare cases, they may experience blood donation reactions such as fainting. If participants experience any physical discomfort, they can contact our researchers at any time, and the medical personnel within the research team will provide timely guidance on post-blood collection reactions.

**10. STATISTICAL CONSIDERATIONS**

**10.1 Intention-to-Treat Set (ITT) Population**

The Intention-to-Treat Set (ITT) is defined as all randomized participants. The primary analysis population for all efficacy endpoints will be the Full Analysis Set (FAS) population.

**10.2 General Considerations**

Summary of participants' demographic and behavioural characteristics. Regarding continuous variables that follow a normal distribution, the mean and standard deviation will be used for description. In the case of variables that do not follow a normal distribution, the median and interquartile range will be used for description. For categorical variables, frequencies and percentages will be provided.

**10.3 Efficacy Analysis**

The following sections provide an overview of the planned analyses for the primary and secondary endpoints of the study's main intervention effects. All intervention effect analyses will be based on the intention-to-treat (ITT) population.

**10.3.1 Outcome Measure**

The primary outcome is the mean changes in the number of HIV tests among TGW during six months of follow-up.

The secondary outcomes include the mean changes in the number of HIV tests during three months, the proportion of HIV testing at six months, the proportion of HIV testing at three months, the mean changes in partner numbers during six months, and the mean changes in the frequency of condomless sex during six months.

We will rely on participants' reports to measure the HIV testing results. Completion of HIV testing is defined as sexual partners undergoing HIV testing based on venue or HIV self-testing (HIVST), uploading the HIVST results via the QR code in the test kit instructions, or directly reporting the HIVST results to the staff.

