**Part B. HIV Testing Behavior**

B1. Have you been tested for the HIV in the past three months? (Single choice)

- Yes
- No

B2. How many times have you been tested for the HIV in the past three months? [fill in the blank]

B3. Have you participated in venue-based (VCT/hospital/CBO workgroup) HIV testing in the past three months? (Single choice)

- Yes
- No

B4. How many times have you been tested for venue-based HIV in the past three months? [fill in the blank]

B5. Have you used HIV self-testing (HIVST) for HIV testing in the past three months? (Single choice)

- Yes
- No

B6. How many times have you used HIVST for HIV testing in the past three months? [fill in the blank]

B7. Have you shared HIVST with your sexual partners in the past three months? (Single choice)

- Yes
- No

B8. In the past three months, which type of sexual partners have you shared HIVST with? (Single choice)

- Regular male sexual partner (i.e., boyfriend or male partner in a stable relationship for at least three months)
- Casual male sexual partner (i.e., non-commercial and non-transactional)
- Commercial male sexual partner (i.e., engaging in sexual activities with male partners in exchange for goods, money, or housing)
- Female sexual partner

B8. How many times have you shared HIV self-testing (HIVST) with your regular sexual partner in the past three months? [fill in the blank]

B9. How many times has your regular sexual partner been tested for HIV in the past three months? [fill in the blank]

B10. In the past three months, are you aware of the HIV infection status of your regular sexual partner? (Single choice)

- HIV negative
- HIV positive
- Not aware

B11. How many times have you shared HIVST with your casual sexual partner in the past three months? [fill in the blank]

B12. How many times has your casual sexual partner been tested for HIV in the past three months? [fill in the blank]

B13. In the past three months, are you aware of the HIV infection status of your casual sexual partner? (Single choice)

- HIV negative
- HIV positive
- Not aware

B14. How many times have you shared HIV self-testing (HIVST) with your commercial sexual partner in the past three months? [fill in the blank]

B15. How many times has your commercial sexual partner been tested for HIV in the past three months? [fill in the blank]

B16. In the past three months, are you aware of the HIV infection status of your commercial sexual partner? (Single choice)

- HIV negative
- HIV positive

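### Section 10.3.1 contradicts itself: the primary outcome is tests among TGW, but the only definition of completed testing names sexual partners and counts a QR-upload route that comes only with the intervention arm's kits

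*Protocol*

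**What the plan says.** Section 10.3.1 states: "The primary outcome is the mean changes in the number of HIV tests among TGW during six months of follow-up". It gives the data source as "We will rely on participants' reports to measure the HIV testing results". The next sentence defines a completed test: "Completion of HIV testing is defined as sexual partners undergoing HIV testing based on venue or HIV self-testing (HIVST"), followed by two further routes, "uploading the HIVST results via the QR code in the test kit instructions, or directly reporting the HIVST results to the staff".

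Under Section 7.4, "the intervention group will have the opportunity to apply for free HIV self-testing (HIVST) kits and mailing services every three months (via WeChat"). A participant may ask for 1 to 5 kits, and Section 3.1 limits the application link to enrolment and month 3. Section 7.4 adds that "they are encouraged to share the HIVST kits with their partners". Kit users may photograph the result and "anonymously upload it to the online platform". Each kit carries a unique code.

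Section 7.2 sends follow-up questionnaires to all participants at three and six months. In Appendix C, Part B, item B2 asks "How many times have you been tested for the HIV in the past three months". B1 asks whether the participant was tested at all, and B3 to B6 split this into venue-based testing and HIVST. Partners' tests have their own items: B9, B12 and B15.

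**The concern.** A definition of a completed test decides what is counted. Here it names people who were not randomised, while the primary outcome and the two testing-proportion outcomes concern the participants. The sentence cannot belong to some other endpoint, because none of the listed primary or secondary outcomes is about partner testing.

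The definition also admits a route that the trial gives to one arm only. Trial kits, and so QR uploads, come with the intervention. These kits may be shared, so an upload need not be the participant's own test. None can exist at baseline, so adding uploads at follow-up would change the measurement over time in one arm alone, in an analysis of change from baseline.

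Two analysts could both follow Section 10.3.1 and build different primary datasets. The trial is open-label, so that choice should be fixed beforehand. The primary test is also the first step of the sequence in Section 10.3.2, so a false positive there opens the later tests.

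**Working it through.** **Side by side**

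| Element | Primary outcome and data source (10.3.1) | Definition of completed testing (10.3.1) |
| --- | --- | --- |
| Whose test | TGW participants | Sexual partners |
| How known | Participants' reports | Venue test or HIVST, QR upload, report to staff |
| Available to both arms | Yes, questionnaires at months 3 and 6 | Venue test: yes. Report to staff: not restricted by arm. QR upload: intervention arm only |

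The two columns disagree on whose test counts, and the protocol gives no rule of precedence between them.

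**The plan's own figure.** Inputs from Sections 10.4 to 10.4.3: difference D = 0.35 tests per three months, sigma = 1, rho = 0.2, M = 2 time points, compound symmetry, two-sided alpha 0.05, power 0.90.

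- SD of a two-time-point mean = sigma × √((1 + (M − 1)rho)/M) = √(1.2/2) = 0.7746.
- n per group = 2 × (0.7746 × (1.960 + 1.2816)/0.35)² = 102.93, so 103. Power at 103 is 0.90019, as stated.
- With 10% dropout: 103/0.90 = 114.4, so 115, as stated.

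The sample size reproduces, and the definition does not affect it.

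**Illustration of what could be at stake.** The documents give no rate at which partner-used kits or uploads would be credited to participants. Let b be an assumed surplus of counted tests per three months in the intervention arm only, with no true effect on the participants' own testing.

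- Standard error of the difference = 0.7746 × √(2/103) = 0.1079.
- False-positive rate = 1 − Φ(1.960 − b/0.1079) + Φ(−1.960 − b/0.1079).
- At b = 0.10: b/0.1079 = 0.926, and the rate is about 15%.

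The last column repeats the calculation for a single time point (SD = 1).

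| Assumed b | Share of 0.35 | False-positive rate, mean of two time points | Same, single time point |
| --- | --- | --- | --- |
| 0.05 | 14% | 7.5% | 6.5% |
| 0.10 | 29% | 15% | 11% |
| 0.15 | 43% | 28% | 19% |
| 0.20 | 57% | 46% | 30% |

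A surplus of 0.10 would arise, for example, if one in ten intervention participants had one extra test credited per three months. These figures use the sample-size model, not the planned covariance analysis, and every value of b is an assumption.

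**The case against.** The strongest reply is that this is one badly worded sentence. The objectives and the primary outcome consistently name TGW, the stated source is participants' reports, and B1 to B6 collect the participant's own tests apart from partners' tests. Both arms are surveyed on the same schedule. All of that stands. A reader might infer that the outcome measures the wrong people, but the documents do not support this: they show a definition that conflicts with the outcome, not an outcome certain to count partners.

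A reader might also infer that the comparison is certainly biased because the routes are unequal. That goes too far. Only QR upload is specific to one arm. Venue testing is open to both, both arms receive a message listing local testing sites (Section 7.3.2), and reporting to staff is not limited by arm. Partners' venue tests, which the literal definition would also count, can occur in either arm. Bias arises only if the definition is applied literally or if uploads or partner tests are added to the questionnaire count, and the protocol does not say that they are.

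Nor do the documents show that a partner's result can never be told from the participant's. Kits carry unique codes, Section 7.6 asks how many kits were shared, and partners who test are invited to complete their own questionnaire. A code identifies the kit rather than the user, however, and no rule says how this information keeps a shared kit out of the requester's count.

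The objection does not remove the contradiction. Nowhere does the protocol say that B2 is the primary count or that it overrides the definition. An analysis plan that is not shown could add detail, but the protocol's stated definition would still be wrong as written.

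**Conclusion.** The point holds as an internal contradiction in the definition behind the primary outcome and the testing proportions. As written, the definition names non-participants and includes a route available to one arm only, and no text resolves the conflict.

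The consequence is conditional: if the definition or the uploads feed the count, partner tests enter the participants' outcome and ascertainment differs between arms, in a direction that could favour HIVST. The size cannot be computed from the documents. The figure of about 15% rests on an assumed surplus of 0.10 tests per three months in the intervention arm, no true effect, and the protocol's sigma of 1, rho of 0.2 and 103 per group. It shows that modest mis-crediting would matter, not that it will occur. No figure stated in the protocol is wrong on this account.

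**What to change.** Replace the definition in Section 10.3.1 with one paragraph that says:

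- A completed HIV test is the participant's own venue-based test or self-test.
- It is counted in both arms from the same month-3 and month-6 questionnaire items: B2 for the number, with B4 and B6 as a consistency check, and B1 for the proportions.
- QR uploads, reports to staff and partner tests do not add to the primary or secondary testing counts and serve only as supportive data.

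The items already exist and the sample size stays at 103 per group, or 115 with dropout. The small cost is that upload data no longer add to the count.
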